## Abstract

**Background:**

Since the COVID-19 pandemic began, there have been concerns that interruptions to the health care system may have led to changes in primary care, especially for care of chronic conditions such as diabetes and heart failure. Such changes may have longer term implications for population health.

**Objective:**

This study aims to describe the impacts of the COVID-19 pandemic on indicators of primary care access, comprehensiveness, and appropriateness among adult patients, as well as on specific indictors of chronic conditions. Additionally, this study aims to determine whether any identified changes were associated with patient sociodemographic characteristics and multimorbidity.

**Methods:**

This is a retrospective, single-arm, pre-post study using Canadian Primary Care Sentinel Surveillance Network (CPCSSN) data. CPCSSN is a research network supported by a primary care electronic medical record database, comprising over 1500 physicians and nearly 2 million patients. We are examining changes in care (eg, frequency of contacts, laboratory tests and investigations, referrals, medications prescribed, etc) among adults. We will also examine indicators specific to evidence-based recommendations for care in patients with diabetes and those with heart failure. We will compare rates of outcomes during key periods of the pandemic between March 13, 2020, and December 31, 2022, with equal time periods before the pandemic. Differences will be examined among specific subgroups of adults, including by decade of age, number of comorbidities, and socioeconomic status. Regression models appropriate to outcome distributions will be used to estimate changes, adjusting for potential confounders. This analysis is part of a mixed-methods study with a qualitative component investigating how patients with diabetes with or without concurrent heart failure perceived the impact of the pandemic on access to primary care and health care–related decisions. This study was approved by the Hamilton Integrated Research Ethics Board (14782-C).

**Results:**

The start date of this study was October 5, 2022, and the prospective end date is January 31, 2024. As of May 2023, the study cohort (n=875,934) is defined, data cleaning is complete, and exploratory analyses have begun. Extended analyses using 2022 data are planned once the new data becomes available. We will disseminate results through peer-reviewed publications and academic conference, as well as creating evidence briefs, infographics, and a video for policy maker and patient audiences.

**Conclusions:**

This study will investigate whether the COVID-19 pandemic has resulted in changes in the provision of primary care in Canada and whether these potential changes have led to gaps in care. This study will also identify patient-level characteristics associated with changes in care patterns across the COVID-19 pandemic. Indicators specific to chronic conditions, namely diabetes and heart failure, will also be explored to determine whether there were changes in care of these conditions.

**Trial Registration:**

ClinicalTrials.gov NCT05813652; https://clinicaltrials.gov/ct2/show/NCT05813652

**International Registered Report Identifier (IRRID):**

RR1-10.2196/49131

## Introduction

The presence of strong primary care systems has been shown to be associated with superior and more equitable health outcomes in the population [1-6]. Core elements of primary care that contribute to population health outcomes include access, continuity, comprehensiveness, coordination, person focus, and equity enhancement [7]. Chronic diseases are common and represent the leading causes of death worldwide [8]. The core elements of primary care make this setting ideal for managing chronic diseases [4,9], and family medicine and other primary care services provide the majority of care for chronic diseases across the lifespan [4,10]. With increasing age, there is an increasing prevalence of multiple chronic diseases [11], and these patients require careful management to reduce morbidity and mortality and improve quality of life [12]. Life-limiting chronic diseases such as chronic obstructive pulmonary disease, heart failure, and chronic kidney disease [13-15] affect millions of people in Canada and are mostly managed in primary care [16-19]. Other conditions that are risk factors for numerous cardiovascular and cerebrovascular diseases (eg, diabetes and hypertension) are associated with poor health outcomes, and these are also managed in primary care [20].

On March 11, 2020, the World Health Organization declared the circulating SARS-CoV-2 as a pandemic. The SARS-CoV-2 pandemic placed a substantial strain on health care services for care of both COVID-19 illness (the majority of which was provided in primary care without need for hospitalization) and non–COVID-19 illness [8,21]. The documented early impacts of the COVID-19 pandemic were reductions in the number of patients visiting primary care offices [22], dramatic increases in remote care especially for older patients [22,23], and new strategies to maintain care such as implementing wellness checks for high-risk patients [24,25].

Early in the pandemic, there were reductions in visits for chronic condition management [20,26,27], preventive screening and diagnostic testing [28,29], and changes in physician referral behaviors [30]. The limited availability of testing and coordination of prevention services was a concern among Canadian family physicians [31]. Professional organizations recommended continuation of in-person care during the pandemic for complex chronic conditions and when physical examination was required; however, many patients avoided seeking primary care, and clinics experienced decreased attendance relating to the care of serious conditions [32,33]. Although telemedicine strategies can be effective for some chronic disease monitoring, patients who experience lack of equity in access to health care are also likely to experience barriers to using technology [34-36].

The onset of the pandemic worsened existing challenges to the prospects of achieving and maintaining an adequate level of comprehensive primary care in Canada. Understanding the ways in which the core functions of primary care [37-39] were affected by the COVID-19 pandemic is essential for chronic condition management and for system assessment overall. Although there are reports that the volume of primary care in Canada has largely returned to prepandemic levels, it is not clear whether and for whom there is a need to “catch up” on care for chronic diseases. For practices with a tendency for overuse of testing and investigations, these may have declined to more appropriate levels during the pandemic, also highlighting the areas of practice improvement. The objectives of this study are to describe the impacts of COVID-19 on chronic disease care and to determine whether changes were associated with patients’ sociodemographic characteristics and multimorbidity.

## Methods

### Data Source

The Canadian Primary Care Sentinel Surveillance Network (CPCSSN [40]) is a multidisease electronic medical record (EMR) research and surveillance data repository that securely collects deidentified health information from EMRs of participating primary care clinicians (eg, family physicians and nurse practitioners) who are referred to as “sentinels.” CPCSSN currently brings together 13 primary care research networks for the purposes of research, disease surveillance, and quality improvement, with more networks due to join in the near future. Every 6 months, CPCSSN acquires deidentified patient-level clinical data from primary care EMR systems held by 1583 primary care providers across Canada, with approximately 200 patient encounters per month per physician [20]. CPCSSN acquires most of the data fields in Canadian primary care EMRs with the exceptions of portable document format such as imaging data and the narrative “Subjective, Objective, Assessment, and Planning” notes. The acquired data are processed into a standard format and are made available for surveillance and research [41]. The relative frequency, longitudinal format, and comprehensiveness of CPCSSN data are ideal for the study of changes in practice, through time, in response to significant environmental imperatives, such as public health or research initiatives [41]. Numerous case definition validation studies have been completed [42-44], and the data have also been used to evaluate patterns and quality of health care [19,45].

### Study Design

This protocol was designed using the RECORD (REporting of studies Conducted using Observational Routinely collected Data) statement [46]. We will conduct a retrospective closed cohort study with a single group using a pre-post design. We will examine prevention and management activities for exemplar conditions on the basis of having a validated CPCSSN case definition [47,48] (ie, diabetes and heart failure), having substantial prevalence in primary care, and either having high morbidity or being risk factors for morbidity if not well managed. Patient-level data extracted from the CPCSSN repository between 2018 and 2022 will be used to investigate changes in rates of presentation and clinical management of various chronic diseases before, and through the phases of, the pandemic.

### Study Population

The study population is all patients who were 18 years and older in 2018, and some analyses will focus on subgroups of patients with specific chronic conditions. We will use the 2-year contact population as recommended previously for defining practice populations for primary care [49]. This method uses contacts within encounter, medication, and billing-related data tables, and has been used previously with CPCSSN data to produce national chronic disease estimates [50]. This method will be used in the period from March 13, 2018, to March 13 2020. We will use this population rather than the full CPCSSN patient population data (dating back more than 2 decades for some networks) to limit the size of the data set, while maintaining the patient population that is likely to have a relationship with a primary care practice during the study period. Although this approach may exclude patients who are younger, healthier, and less likely to seek primary care compared with patients with chronic conditions, we do not expect this to have a major impact on findings because this study focuses on the age group where chronic condition prevalence begins to increase and where screening guidelines apply (eg, diabetes). Therefore, this age group is more likely to see a primary care physician regularly.

People who died during the study period will be included up to the point of death using the death date if captured or the presence of a deceased status with date estimated from the most recent contact in CPCSSN data. Patients who were older than 105 years at the start of the COVID-19 pandemic will be excluded as a possible data error.

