### Variables of Interest

#### Primary Exposure

The primary exposure is the start of the pandemic in March 13, 2020. This date was selected as it marks the beginning of Canadian provincial governments responding to the formal declaration of the pandemic by the World Health Organization on March 11, 2020, by enforcing sweeping public health and safety measures. The prepandemic time frame used is defined as June 22, 2018, through March 12, 2020. The pandemic time frame used in this study runs from March 13, 2020, through December 31, 2022. In addition to comparison between these 2 periods, 30-day interval rates will also be calculated for selected outcomes and indicators where possible.

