^q^NRT: nicotine replacement therapy.

*Access* to the practice will be measured as the overall number of encounters.

*Comprehensiveness* refers to primary care addressing “all problems in the population (with short-term referral as needed), except those that are too unusual (generally a frequency of less than 1 or 2 per thousand in the population served) for the primary care practitioner or team to treat competently” [1]. As indicators of comprehensiveness, we will measure number of different diagnoses addressed per patient per year, proportion of patients’ chronic conditions addressed at least once a year, number of pneumococcal vaccines and influenza vaccines in patients 65 years or older, and number of prescriptions for nicotine replacement therapy

*Appropriateness* will be examined in 2 ways: laboratory tests that are indicated for monitoring of chronic conditions but may be ordered more frequently than necessary (eg, hemoglobin A_1c_ in diabetics) and laboratory tests that are frequently ordered routinely (or for screening purposes) but may be overused in certain populations, including thyroid function tests, vitamin D, albumin-to-creatinine ratio, and lipid panel testing [53]. We hypothesize that some of these tests, while indicated at a base frequency, may be commonly overused; thus, their frequency may have declined during the pandemic.

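### Cohort entry selects patients on prepandemic contact but not on pandemic contact, so the paired pre-post contrast leans toward a decline even if nothing changed

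*Protocol article*

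**What the plan says.** Study Design in the protocol article sets the frame: "We will conduct a retrospective closed cohort study with a single group using a pre-post design". Study Population defines entry: "We will use the 2-year contact population as recommended previously for defining practice populations for primary care". It adds that "This method uses contacts within encounter, medication, and billing-related data tables", and fixes the dates: "This method will be used in the period from March 13, 2018, to March 13 2020".

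Primary Exposure fixes the compared periods: "The prepandemic time frame used is defined as June 22, 2018, through March 12, 2020", and "The pandemic time frame used in this study runs from March 13, 2020, through December 31, 2022". Under Outcome Definitions and Measures, access "will be measured as the overall number of encounters". Table 1 draws that outcome from the encounter, encounter diagnosis and billing tables. Analyses of Changes Over Time compares the cohort with itself by McNemar, Wilcoxon signed rank and paired *t* tests, followed by regression on age, sex, comorbidity count, income quintile and network.

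Study Population acknowledges that the rule may leave out younger and healthier people and expects no major effect. The Sensitivity Analysis section and the limitations deal with representativeness. None of these mentions that the entry rule acts on one side of the comparison only.

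**The concern.** A patient enters by having a contact at a time that is almost all prepandemic outcome time. Contacts are also the access outcome, and most other indicators can be recorded only if a contact occurs. Entry therefore conditions on the outcome before March 2020 and imposes nothing after it. Someone who attends rarely and happened to attend in 2019 is in the cohort. Someone with the same underlying rate who happened to attend only in 2021 is not. The later period then shows regression to the mean.

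The listed covariates cannot remove this, because the selection is on the pre-period outcome itself. Matching the sample to the Canadian population leaves the entry window unchanged.

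At stake is whether a modest or lasting fall in encounters, blood pressure measurement or testing is read as a care gap, or as reduced overuse of tests. The artefact also differs between groups with different contact rates, so it can distort comparisons by age, comorbidity and socioeconomic status.

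**Working it through.** **1. The plan's own figure.** Statistical Analysis and Power gives 1276 pairs for 50% to 55% at correlation 0.2, and 1432 at 0.1. Two-sided 5% and 80% power are assumed, since the article states neither.
- ψ = 0.5×0.45 + 0.55×0.5 − 2×0.2×√(0.25×0.2475) = 0.4005.
- n = (1.96√ψ + 0.8416√(ψ − 0.0025))²/0.0025 = 1255. Adding 1/0.05 = 20 gives 1275.
- At correlation 0.1: 1411 + 20 = 1431.

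The stated sizes reproduce to within rounding, and this point does not affect them.

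**2. Windows, from the stated dates.**
- Entry: March 13, 2018 to March 13, 2020 = 732 days.
- Prepandemic: June 22, 2018 to March 12, 2020 = 630 days, all inside the entry window.
- 732 = 101 days before the prepandemic period + 630 + 1 day shared with the pandemic period.

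**3. Contact rate (assumed, bracketed from the article).** Data Source gives 1583 providers and about 200 encounters per month each: 1583 × 200 × 12 = 3,799,200 per year. Divided by about 2 million patients this is 1.9 per year; by 1.13 million adults, 3.4; by the cohort of 875,934, 4.3. I use 2 to 4.

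**4. Null model.** Each patient has a constant rate drawn from a gamma distribution with mean m and shape k, and Poisson contacts. There is no pandemic effect, nobody joins or leaves, and the two periods are of equal length (the Abstract promises equal periods). Let b = k/m, T = 731/365.25 = 2.00 years (dropping the one shared day), and q(t) = (b/(b+t))^k, the probability of no contact in t years.
- Share selected: 1 − q(T).
- Relative change in mean contacts: −(b/(b+T))^(k+1).
- Change in a 12-month proportion recorded at a fraction p of contacts: −[q(T) − q(T+p)]/(1 − q(T)).
- Share of the cohort with no prepandemic contact: [q(630 days) − q(T)]/(1 − q(T)).

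Example, m = 3, k = 1: b/(b+T) = 0.333/2.335 = 0.143, and its square is 0.020, so mean contacts fall 2.0%. With p = 0.5: (0.1428 − 0.1176)/0.857 = 0.029, a fall from 70.0% to 67.1%.

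| Contacts/year | Shape | Mean encounters | 12-month proportion, p = 0.3 | p = 0.5 |
|---|---|---|---|---|
| 2 | 0.5 | −3.7% | −3.0 points | −4.8 points |
| 2 | 1 | −4.0% | −2.7 | −4.2 |
| 2 | 2 | −3.7% | −2.2 | −3.3 |
| 3 | 0.5 | −2.1% | −2.4 | −3.8 |
| 3 | 1 | −2.0% | −1.9 | −2.9 |
| 3 | 2 | −1.6% | −1.3 | −1.9 |
| 4 | 0.5 | −1.4% | −2.0 | −3.2 |
| 4 | 1 | −1.2% | −1.5 | −2.3 |
| 4 | 2 | −0.8% | −0.8 | −1.3 |

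The share with no prepandemic contact is 1.1% to 3.4%.

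**5. Who is affected.** At 1 contact per year (shape 0.5 to 2), mean contacts fall 9% to 12.5%. At an assumed 6 to 8 per year (shape 2), they fall 0.1% to 0.3%, and the 12-month proportions fall 0.3 to 0.7 points.

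**6. Significance.** A simulation started with 875,934 patients at 3.4 contacts per year and shape 2 selected 831,058. Mean contacts fell 1.2% with no true change, and the paired *t* was about −20.

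**7. Moving the entry contact.** If entry is decided outside both compared periods, a constant rate gives two equal-length periods the same expected outcome, so the artefact is zero by construction. Simulating entry by a contact from March 13 to June 21, 2018 gave counts within 0.2% and any-contact shares within 0.1 point of equality.

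**The case against.** The other side is strong on size. The most striking figure available is the share with any contact in 630 days, which in this model falls by 2.7 points (98.9% to 96.2%) to 12.4 points (96.6% to 84.2%). A reader might set that against the 5-point change used for planning. Table 1 lists no such outcome. Access is a count, and the 12-month proportions in the table above stay below 5 points.

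A reader might also infer that the rule guarantees prepandemic care. It does not. A qualifying contact may fall in the 101 days before June 22, 2018, and a contact guarantees no particular test, reading or referral.

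The bias is smaller in diabetes and heart failure, the exemplar conditions, if those patients attend more often, as is likely but not documented. Comparisons between pandemic phases all come after selection and escape this mechanism.

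Joining and leaving also matter. Patients who joined during 2018 to 2020 have shortened prepandemic time. With 5% per year joining (assumed), the net change in mean count ranges from −0.9% to +2.2%. With 5% per year also leaving unrecorded, it is about −6% to −9%. The net bias in raw counts therefore depends on observation time as well. The article says "People who died during the study period will be included up to the point of death using the death date if captured"; rules for other exits may sit in a fuller plan, and their absence is not counted here.

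Finally, the two-year rule is a recognised, reasoned choice. That defends it as a definition of a practice population, but not the one-sided overlap.

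**Conclusion.** The point stands as a bias of modest size that should be corrected. The overlap follows from the stated dates alone. The direction of the selection effect does not depend on the assumed rates or dispersion. Its size does: about 1% to 4% for mean encounters, and about 1 to 5 points for 12-month proportions recorded at 30% to 50% of contacts, assuming 2 to 4 contacts per year, shape 0.5 to 2 and a stable attached population. Selection on prepandemic contact is near-complete, not absolute.

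A reader might go further and conclude that the pre-post comparison is invalid or the closed cohort must be abandoned. The documents do not support that. A large early-pandemic fall would far exceed this artefact. What is not secure is a claim of a modest or persisting gap, or of a small subgroup difference, and at this sample size a significant *P* value gives no protection.

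**What to change.** Keep the closed cohort and add an analysis in which the entry contact precedes and overlaps neither compared period.

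- **With the data in hand:** require a contact from March 13 to June 21, 2018. These dates fall within the planned 2018 to 2022 extraction. This also removes patients who joined part-way through the prepandemic period.
- **Where networks hold earlier data:** use a contact in the 24 months before June 22, 2018, or a prepandemic comparison cohort entered at the same lag as the pandemic cohort, analysed with patient-level GEE because most patients would appear in both.
- **Denominator:** use observed person-time with a stated end of observation. Under an assumed 5% per year unrecorded departure, moving the entry window alone still left raw counts falling about 8%; rates on observed person-time brought this to about zero.
- **Interpretation:** base conclusions about modest declines and subgroup differences on agreement between the two analyses, and state the asymmetry as a limitation.

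Cost: in the model above, the 101-day entry keeps 44% to 61% of the present cohort and tilts it to frequent attenders (at m = 3, k = 1, mean rate 4.6 per year against 3.4). It therefore complements the main cohort and does not replace it. The 24-month version needs a further data request and cleaning, and networks without earlier history drop out of it.

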#### Analyses of Changes Over Time

We will present the proportions of patients experiencing the outcomes for each time period or mean changes for continuous variables and 95% CIs. Statistical significance of changes from pre to post time period will be assessed using the McNemar test for binary variables, the Wilcoxon signed rank test for original variables, and the paired *t* test for continuous variables. Regression models appropriate to outcome distributions will be used to control for potential confounders of age (<70 vs ≥70 years), sex, count of comorbidities (CPCSSN-validated conditions), neighborhood income quintile, and CPCSSN network (corresponding to location within Canada). Interactions will be examined in the descriptive analysis and will be considered for inclusion in models if they are found to be relevant. We will present adjusted estimates and 95% CIs for outcomes and parameter estimates for the independent variable and covariates. Analyses will be completed using SAS (version 9.4; SAS Institute, Inc).

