### Future Analyses

We will attempt to extend our analyses to include the first half of 2022 when data become available if our timelines and resources allow. At the time of writing this protocol (May 2023), data were available up to December 2021. The additional 2022 data will allow us to investigate changes in primary care in the later portion of the COVID-19 pandemic, capturing the Omicron wave, and measure whether any changes identified in the earlier portion of the pandemic were sustained or returned to prepandemic patterns of care.

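### Decedents get partial follow-up, but the paired pre-post tests are tied to no observed time, so the 6- and 12-month indicators may show death or departure as lost care

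*Protocol article*

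**What the plan says.** Study Design: "We will conduct a retrospective closed cohort study with a single group using a pre-post design".

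Study Population bases entry on a contact with the practice over two years: "This method will be used in the period from March 13, 2018, to March 13 2020". It gives one rule for leaving observation: "People who died during the study period will be included up to the point of death", by the recorded death date where there is one. Where only a deceased status is recorded, the date is estimated from the latest contact. The article states no rule for patients who change practice or for practices that stop contributing.

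Primary Exposure fixes the windows: "The prepandemic time frame used is defined as June 22, 2018, through March 12, 2020" and "The pandemic time frame used in this study runs from March 13, 2020, through December 31, 2022". Future Analyses adds that at the time of writing "data were available up to December 2021".

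Analyses of Changes Over Time says that significance of pre-post change "will be assessed using the McNemar test for binary variables", with the Wilcoxon signed rank and paired t tests for other variable types. Regression models follow, with the family left open. Thirty-day rates are planned for selected outcomes. No denominator or offset is named for either.

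Many Table 1 indicators use fixed intervals: diabetes- or heart-failure-related encounters and blood pressure measurement every 6 or 12 months, HbA1c every 6 and 12 months, and foot examination within 12 months.

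**The concern.** Two stated choices do not fit together. The inclusion rule lets a decedent contribute part of a period. The named tests take one value per person per period. A patient who dies a month into the pandemic has a month of follow-up to set against 630 days before. For a 12-month binary indicator, McNemar's test must either treat that truncated window as complete, so that an unmet indicator looks like missed care, or lose the pair, which drops someone the plan says to include. A patient who dies before March 13, 2020 has no pandemic value at all.

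Entry depends on a contact before the pandemic, so exits fall more heavily on the pandemic side. On a fixed-interval proportion, an absence scored as a miss can only lower the result. Deaths concentrate in older and sicker patients, the groups whose care gaps the study wants to compare, so differential mortality could be reported as differential loss of care.

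**Working it through.** **Benchmark: the plan's own effect size.** Statistical Analysis and Power gives 1276 pairs (correlation 0.2) and 1432 pairs (correlation 0.1) for a change from 50% to 55%. Alpha and power are not stated; I assume two-sided 0.05 and 80%.

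- Discordant share: pd = p1(1−p2) + p2(1−p1) − 2ρ√(p1q1p2q2), with q = 1 − p. At ρ = 0.2: 0.225 + 0.275 − 0.4 × 0.2487 = 0.4005.
- n = [1.960√pd + 0.842√(pd − d²)]² / d², with d = 0.05, gives 1255.0. Adding 1/d = 20 as a continuity correction gives 1275.0.
- At ρ = 0.1: 1411.2 + 20 = 1431.2.

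The stated figures reproduce to within rounding. The useful benchmark is the 5-point change.

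**Windows.** June 22, 2018 to March 12, 2020 is 630 days. March 13, 2020 to December 31, 2022 is 1,024 days (T = 1024/365.25 = 2.80 years). To December 31, 2021 it is 659 days (T = 1.80 years).

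**Person-time lost to death.** With constant mortality m per year, everyone alive on March 13, 2020 and no other exit, the share of the window observed is (1 − e^(−mT))/(mT). The article gives no m, so the values below are assumptions.

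| m per year | observed, 1,024 days | lost | observed, 659 days | lost |
|---|---|---|---|---|
| 5% | 0.933 | 6.7% | 0.956 | 4.4% |
| 10% | 0.872 | 12.8% | 0.915 | 8.5% |
| 15% | 0.816 | 18.4% | 0.876 | 12.4% |

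If counts are divided by the full window instead of observed time, the mean rate falls by the lost share with care unchanged.

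**Fixed-interval proportions.** Suppose care is unchanged, the baseline is 50%, and a share f of patients is gone and scored as not meeting the indicator. The false fall is 0.5f: 0.5, 1.0, 2.5 and 5.0 points for f = 1%, 2%, 5% and 10%. At f = 10% it equals the change used for the sample size.

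For f = 2% and ρ = 0.2, p falls from 0.50 to 0.49, pd = 0.400 and z = 0.01/√(pd/n):

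- whole cohort, n = 875,934: z ≈ 14.8
- diabetes at 10%, n ≈ 87,593: z ≈ 4.7
- heart failure at 4%, n ≈ 35,037: z ≈ 3.0

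**Raw counts.** 1024/630 = 1.63, so an unstandardised count rises about 63% with unchanged care and no exits. With the assumed mortality it still rises: 1.625 × 0.933 = 1.52, 1.625 × 0.872 = 1.42 and 1.625 × 0.816 = 1.33. With data to December 2021 the ratio is only 659/630 = 1.046, and the products are 1.00, 0.96 and 0.92. The net direction for raw counts therefore depends on where the data end.

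**The case against.** Several stronger readings are tempting, and the document does not support them.

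- **That the plan counts the dead and departed as uncared for.** It never says how a truncated window is scored. Its rule for decedents points towards time-limited contribution, and dropping incomplete pairs is another possible reading.
- **That nobody but decedents is censored.** This is silence in a condensed article. Rules for transfers and practice exit commonly sit in a fuller document, so their absence is not a fault here.
- **That paired tests cannot use partial follow-up.** For counts they can: Wilcoxon and paired t tests may be run on each patient's annualised rate. The difficulty is sharpest for McNemar's test on interval indicators.
- **That no analysis carries time.** The article refers to rates, per-year measures and 30-day intervals, and its regression models could take an offset.
- **That every outcome is biased towards decline.** Raw counts over 630 and 1,024 days move upward. The Abstract speaks of equal comparison periods, which would remove that push. Blood pressure control need not include unmeasured patients, and the Discussion treats a fall in overused tests as possibly appropriate.
- **That all loss falls in the pandemic period.** Patients can die or leave between entry and March 2020. The loss is heavier later, but not confined there.

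These objections narrow the point without removing it. The decedent rule and the unadjusted tests are both stated, and nothing in the article connects them through observed time.

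**Conclusion.** The point holds as a mismatch between the follow-up rule for decedents and the paired tests. It matters most for the 6- and 12-month proportions and for rates divided by full calendar time. There the risk is an apparent loss of care that is really loss of observation, larger in older and sicker groups.

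Its actual size cannot be known from the article. The 7%, 13% and 18% losses of person-time (4%, 8.5% and 12% to December 2021) rest on assumed mortality. The false falls in proportions rest on an assumed share of patients gone and on their being scored as misses. In a cohort of 875,934, statistical significance offers no protection: under those assumptions, a 1-point artefact is significant even in heart failure. The point calls for a correction before the main analyses and does not invalidate the design.

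**What to change.** - Analyse counts per observed time: Poisson or negative binomial GEE with log observed days as offset, or paired tests on annualised rates.
- For each 6- or 12-month indicator, limit the denominator to patients alive and observable for the whole interval.
- State that observation ends at death and, where the repository holds the dates, at recorded departure or the practice's last data extraction. The article does not say whether it holds them.
- Add a sensitivity analysis in practices contributing throughout both periods.
- Add another that varies the end date for decedents whose death date is estimated from their last contact. Ending follow-up at a contact inflates their rates, so an offset alone would replace one bias with another.

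The cost is analysis wording, some date derivation and a small loss of patients from the interval indicators. Those indicators will then describe people who remained observable through the interval, and reports should say so. The data are retrospective and only exploratory analyses had begun by May 2023, so no new data collection is needed.
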